**Fig. 2 Fig2:**
[figure not shown]
CONSORT Flow diagram of study design

### Study setting

The study will take place in the Health Service Executive Mid-West region of Ireland in pre-existing community sport and physical activity hubs that were developed as part of Ireland’s national physical activity plan and whose purpose is to increase engagement in physical activity generally and particularly amongst disadvantaged, marginalised and hard to reach groups. A total of eight hubs across Clare (*n* = 4) and Limerick (*n* = 4) will be enrolled. Data collection will be entirely completed in a community setting, using the community or parish halls in which the exercise programmes are conducted. The study is being conducted by a multidisciplinary team from the University of Limerick, Faculty of Education and Health Sciences, and the Local Sports Partnerships, in collaboration with NUI Galway, Health Services Executive Health and Wellbeing, Healthy Ireland, Age and Opportunity and Clare, Limerick city and county councils.

### Sample size justification

As this is a feasibility study, a formal sample size calculation has not been used but the sample size was estimated based on the primary outcome of interest, which is the feasibility of measuring MVPA. The minimum numbers required to sustain structured physical activity programmes and necessary group dynamics. Each programme involves an instructor working with a group and, for feasible group dynamics, requires between 12–15 inactive adults. If each hub involves four physical activity programmes, it will give a sample of 48–60 participants per hub—a total of 480 participants. Allowing for a 20% dropout rate, an additional 96 people will be recruited giving a maximum sample of 576.

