**Methods:**

The trial is set in eight Local Sports Partnership (LSP) hubs that have structured physical activity programmes. The hubs are the units of randomisation (clusters), and individuals are the units of analysis (participants). Eligible participants will contact one of the hubs, with each hub running four physical activity programmes. Each programme requires between 12–15 inactive adults, resulting in 48–60 participants per hub. Allowing for 20% dropout rate, an additional 96 people will be recruited giving a maximum sample of 576. The hub will be randomised: true control, usual programme or MFL intervention. The true control group will be given information about physical activity but will not be included in a programme for the duration of the trial; the intervention will involve the instructor training one (or more) of the participants to be a peer mentor using an educational toolkit; and usual care groups will have physical activity classes delivered as normal. Baseline data will collect physical activity measures and follow-up measurements will be obtained at 3 and 6 months. All participants will be asked to wear a device for measuring activity on the thigh (activPAL) for 7 days before commencing the programme and at 3 and 6 months. The primary objective of the study is to investigate if it is feasible to deliver the intervention and collect data on moderate to vigorous physical activity (MVPA) on all participants, thereby providing valuable information to guide sample size calculation for a future, more definitive trial.

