### Study design

Move for Life is a feasibility cluster randomised control trial (RCT) where the LSP hubs are the units of randomisation (the clusters), and individuals within the hubs are the units of analysis (the participants). The advantage of a cluster RCT is that it overcomes contamination problems that arise if a simple random allocation is used. When testing a complex intervention, randomisation of participants risks contamination if individuals from both arms attend the one group. This study will enrol a total of eight hubs and randomise physical activity groups to each of three arms. This framework is in line with the recommendations of Eldridge et al. [20] and the CONSORT [19] guidance on the minimum number of clusters required to obtain accurate estimates of rates and proportions in pilot and definitive cluster RCTs, respectively. The first arm is the Move for Life intervention (three hubs), the second is the usual programme (three hubs) and the third is the true control (two hubs).

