## Discussion

Participant recruitment is an essential consideration for the MFL feasibility study. Accordingly, several meetings were held to develop the recruitment strategy. The important questions were what strategies to use for recruitment, what days and times would best suit potential participants for recruitment events and how long before the commencement of the trial should recruitment begin. Further challenges envisaged regarding recruitment are that it may be difficult to attract older adults under the age of 60 years who may be working and who may not identify as being ‘older adults’.

It may be difficult to appeal to all these age groups using the same recruitment strategy, terminology and imagery. Furthermore, it may be difficult to convince health care professionals that the interventions are safe and effective for their patients and that may present a recruitment challenge. Consequently, we have involved clinical members of the research team in the recruitment.

There were also questions about numbers of physical activity programmes within each hub and if adequate numbers were not found to run a particular type of programme, what would happen. The team agreed that all hubs would not necessarily have the exact same number of programmes (some may run with three and others with four, depending on demand). There was also the question of participant preference regarding physical activity programmes. The team agreed that at the screening event, participants would be asked to rank the activity programmes in order of preference and they would be advised that they could not be guaranteed their first preference but every effort would be made to accommodate them.

There were several other points of concern for the research team. Ideally, there would have been stratification in the randomisation process in terms of hub profile: social status, age and gender. After discussion with feasibility trial experts, the team decided to stratify along urban-rural lines only. In Limerick, there are two urban and two rural hubs and, in Clare, there are two rural and two urban hubs. The research analysis team will be blinded. It will be necessary to be aware of concealment at meetings and to conceal information regarding the hubs from the analysis team.

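### The stated total of 480 is only the top of a 384–480 range, and the 20% dropout allowance is taken on the wrong base: 576 recruits leave about 461, not 480

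*Protocol article*

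**What the plan says.** The Sample size justification states that "a formal sample size calculation has not been used", and in the same sentence that "the sample size was estimated based on the primary outcome of interest, which is the feasibility of measuring MVPA". The figures that follow come from class logistics. A programme needs 12–15 inactive adults for workable group dynamics, and: "If each hub involves four physical activity programmes, it will give a sample of 48–60 participants per hub—a total of 480 participants". The dropout step is: "Allowing for a 20% dropout rate, an additional 96 people will be recruited giving a maximum sample of 576".

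The Methods part of the Abstract repeats the 48–60 per hub, the 96 and the 576: "Allowing for 20% dropout rate, an additional 96 people will be recruited giving a maximum sample of 576". It does not repeat the 480.

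Study design fixes the number of hubs at eight: three for Move for Life, three for the usual programme and two for true control. The Discussion relaxes the four programmes per hub: "some may run with three and others with four, depending on demand".

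**The concern.** Three things do not fit together. A range per hub becomes a single total with no lower end. The dropout allowance is a percentage of the number to be kept, when dropout is a percentage of the number recruited. And the maximum sample, spread over the planned classes, gives an enrolment size above the 12–15 in the same paragraph, which does not say whether 12–15 describes a class at its start or after losses.

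The stated basis is also inaccurate. The paragraph says the size was estimated from the feasibility of measuring MVPA, but none of its figures comes from that outcome.

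Recruitment, retention and attrition are among what this study sets out to report. Readers will naturally set the results beside the planned numbers, so those numbers should agree with one another.

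**Working it through.** **Inputs.** Eight hubs (Study design). Four programmes per hub, 12–15 adults per programme, 20% dropout, 96 added, maximum 576 (Sample size justification). Some hubs may run three programmes (Discussion).

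**Reproducing the plan's figures.**
- 8 hubs × 4 programmes × 15 = 480. This matches only with the upper class size.
- 20% of 480 = 96, and 480 + 96 = 576. This is 480 × (1 + 0.20), so the route to 576 is clear.

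**The total.**
- Lower end: 8 × 48 = 384.
- Upper end: 8 × 60 = 480.
- Each hub that runs three programmes lowers the range by 12–15. With one such hub it is 31 × 12 = 372 to 31 × 15 = 465.

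**The dropout allowance.** If a proportion d of those recruited drops out, keeping n requires n/(1 − d).
- 480/(1 − 0.20) = 600, against the stated 576.
- 576 × (1 − 0.20) = 460.8, about 461.
- 480 − 461 = 19, and 19/480 = 4.0%.
- 96/576 = 16.7%, so the added 96 offset a 16.7% loss, not 20%.

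**Class size.**
- 8 × 4 = 32 classes.
- At enrolment: 576/32 = 18.
- After 20% dropout: 460.8/32 = 14.4.
- With one hub running three programmes: 576/31 = 18.6 at enrolment.

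The two true-control hubs hold no classes during the trial, so 18 is a running class size only in the other six hubs. The average there is the same if recruits are spread evenly: 576 × 24/32 = 432, and 432/24 = 18.

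**The case against.** The strongest reply is that this is a feasibility study with no formal calculation, so a gap of 19 people costs nothing, and that the article calls 576 a maximum, which partly signals that upper bounds were used. Most of this stands. No power is lost, 461 lies within 384–480, and the thresholds under Progression criteria are percentages that use neither 480 nor 576. The reply does not explain why 48–60 per hub yields a single total, and it does not make 576 the right allowance for a 20% loss from 480.

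Several stronger readings are tempting, and the article does not support them:

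- **Classes outside the plan's viable range.** A reader might infer this from 18 against 12–15. But the paragraph speaks of minimum numbers needed to sustain a programme, which fits a size to be kept after losses at least as well as a limit at enrolment. On that reading 14.4 is inside the range. The text is unclear here, not shown to be in breach.
- **An overstated number of completers.** The article never promises 480 completers. That 480 was to be retained is a fair inference from allowing for dropout, but only an inference.
- **A floor of 288.** This needs all eight hubs to run three programmes (8 × 36). The Discussion says only that some may.
- **Control hubs beyond the class-size argument.** Under Randomisation process, their participants wait and are offered the programmes after the trial, so class-sized groups have a rationale there too.

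**Conclusion.** The figures are wrong as written. The total should be 384–480 with four programmes per hub. An allowance of 96 does not cover 20% dropout from 576: it leaves about 461, and 600 would be needed to keep 480. The class size of 12–15 needs a time point, because 576 implies 18 at enrolment and 14.4 after dropout. The statement that the primary outcome set the size does not match the inputs used.

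The shortfall figure rests on two assumptions: that the 20% applies to all who are recruited, and that the purpose of the allowance was to retain 480. The class averages assume that recruits are spread evenly over 32 classes. This is a minor correction, which does not call into question the design, the progression criteria or what the trial can estimate.

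**What to change.** Restate the Sample size justification, and bring the Abstract into line with it:

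1. Give the total as 384–480 with four programmes in each of eight hubs, and note that it is lower where a hub runs three.
2. State that recruiting a maximum of 576 leaves about 461 at 20% dropout.
3. Say that 12–15 is the class size after dropout, with up to 18 at enrolment, or otherwise reconcile the two figures.
4. Say that the size was set by class logistics, and remove the claim that it was estimated from the feasibility of measuring MVPA.

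The cost is a few reworded sentences. The maximum of 576 can stand, and no participants are added or removed.

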### Participants: eligibility and recruitment

Recruitment will start 8 weeks before the trial commences. The study aims to recruit inactive, harder to reach groups including ethnic minorities, people less inclined to group participation and those that are socially excluded. ‘Physically active’ is defined by the national Physical Activity Guidelines (PAGL) as 150 min of physical activity of at least moderate intensity per week [21, 22]. All potential participants will be asked to complete a short two-item self-report physical activity screening questionnaire [23]. Those who are aged over 45 and who report less than 150 min of MVPA will be invited to participate in the physical activity programme. The cut-off range of 45 years was chosen as it became apparent that few adults aged between 50 and 60 were registering an interest in participation when the study was advertised for ‘older adults’. The trial will be restricted to adults aged 50 +. Also, potential participants must be able to undertake exercise independently.

The study collaborators, Limerick and Clare Local Sports Partnerships, Healthy Limerick, Age Friendly Limerick/Clare and the Health Services Executive, Age and Opportunity, will assist with recruitment. These collaborators have committed to recruiting participants through community networks and have an established track record in recruiting inactive adults aged fifty and over. Further recruitment through the media, local parish newsletters, sports and community organisations including sports clubs like the Gaelic Athletic Association, active retirement group and others will be involved in recruitment. Non-traditional recruitment methods including liaison with local charities and advertisements with mental health services will be used to recruit marginalised groups. Primary health care professionals including GPs, physiotherapists, pharmacists and nutritionists will be incorporated into the recruitment strategy. Evidence suggests that advice from these groups promotes engagement in physical activity programmes [24–27]. An official MFL launch, addressed by the president of the university and a government minister, will take place 2 weeks prior to trial commencement and will receive local and national media coverage. Social media will also be used and MFL Twitter and Facebook accounts will be used for recruitment.

The inclusion and exclusion criteria for the trial are listed below:

Inclusion criteria:Inactive adults, i.e. adults who self-report that they do not meet the PAGL of 150 min of exercise moderate to vigorous physical activity per weekCommunity dwellingAge 50 years and overAble to exercise independently

Exclusion criteria:Aged under 50 yearsActive adults, as defined aboveUnable to exercise independently

### Randomisation process

The hubs will be the unit of randomisation and will be randomised to each arm. Each hub (cluster) will be geographically separated to reduce contamination effect. Clusters will be stratified as rural or urban. Hubs will be randomised to one of the following: true control (two hubs), usual programme (three hubs) or MFL intervention (three hubs). Participants in the true control group will be given information about physical activity but will be placed on a waiting list for access to the MFL physical activity programmes for the duration of the trial. They will be offered the programmes after the trial. The participants allocated to the MFL intervention group and the usual physical activity programmes will not be aware of their status. Randomisation will only occur and will only be revealed to participants and their instructors after all the baseline data have been collected.

### Description of comparator intervention

The physical activity programmes in the comparator intervention will be run by the LSPs at existing exercise hubs in community settings. The programmes were developed as part of Ireland’s national physical activity plan, ‘Get Ireland Active’ [28]. These programmes run nationally and their purpose is to encourage and support physical activity by facilitating access to a wide range of physical activity opportunities in local communities. For Move for Life, four existing LSP programmes were identified as suitable for inactive adults aged 45 + years. Two programmes are gender segregated: ‘Men on the Move’ and ‘Women on Wheels’, both are 12-week structured exercise classes involving general sport, physical activities and cycling. ‘Get Ireland Walking’ is an 8-week walking initiative for inactive men and women; ‘Go for Life’ is an 8-week structured exercise class that typically recruits older adults aged 65 years plus. For the purposes of the comparator intervention in this trial, these programmes will run in the usual way so that participants are exposed to a community-based structured physical activity programme. Participants in the intervention arm of the trial will have these programmes augmented by the Move for Life intervention.

### Development of the intervention

Three hubs will be allocated to the MFL intervention arm. Documents relevant to the four LSP programmes to be augmented for MFL were examined. In 2018, a qualitative study, involving stakeholders in current community exercise programmes, was conducted to investigate factors that affect recruitment, retention and scalability of these programmes.

Using the sources outlined, the MFL intervention was designed on a foundation of theoretical, empirical and practical information. The intervention mapping approach was used to identify theory-based determinants and matching them with appropriate methods for change [29]. A toolkit in the form of a training manual has been developed to train MFL professional instructors in key behaviour change techniques, involving social support and group dynamic strategies along with behavioural skills, aimed to facilitate change and maintenance of physical activity over time. The MFL toolkit contains strategies and outcomes identified in the intervention mapping process. The process will be described in more detail in a separate paper. Social cognitive theory (SCT) [30] was the primary conceptual framework of the intervention because of its emphasis on self-efficacy and social support. Behavioural skills strategies to address outcome expectancy and self-efficacy determinants of behaviour were derived from previous SCT-based intervention work [31, 32] The Theory of Planned Behaviour [33], a second conceptual framework, guided the intervention design in terms of influencing participants’ attitudes and beliefs around physical activity. Self-determination theory (SDT) [34] was a third conceptual framework, using its focus on basic psychological needs for autonomy and relatedness to others to having a positive impact on desired behavioural outcomes [35]. A fourth conceptual framework, the model of group cohesion in exercise and sport [36], was employed, with particular emphasis on task cohesion (i.e. how well participants work together toward a common goal) and social cohesion (i.e. how much participants enjoy working with each other toward the goal) to develop strategies for the group to achieve its outcomes.

It was initially envisaged that the Local Sports Partnerships (LSP) tutors would identify a suitable non-professional volunteer from existing programmes to act up as a peer mentor for this study. The desirable criteria were strong motivation and interpersonal skills and experience with group dynamics. However, because of challenges recruiting in this way and concerns about upsetting the group with an ‘outsider’ as a peer mentor, it was decided to recruit the peer mentor from the groups during the trial. Part of the role of the LSP tutor facilitating the programme would be to identify participants suitable for the peer mentor role*.*

A team of educational experts with experience in physical activity and behavioural change will provide the peer mentor training through a series of interactive workshops. The peer mentors will be identified by the LSP sports development officer in the early stages of the Move for Life trial and will receive training during the course of the programme. They will be trained in motivational change techniques so that they will be able to develop rapport with their peers and to support and encourage them in their journey to become more physically active. They will be trained on group dynamics, how to access local assets and facilities, to access funding by applying for grants and to promote their group by social and local media so as to secure the sustainability of the programme. During the trial, they will have the support of the sports development officer and, thereafter, peer mentors will be provided with leadership training courses and linked with local community organisations, including the LSPs.

The MFL peer mentor will receive training from the MFL team, which will provide advice on how to maintain the group post 8/12 weeks formal programme. This training will provide information and organisational support and identify social and environmental supports for physical activity locally. Additionally, during the MFL programme, individuals who show an interest in helping to sustain the programme, post involvement of the professional, will be identified by the MFL instructor and the peer mentor, and these emerging assistants will be provided with support to contribute to the sustainability of the programme. At the end of the MFL programme, the assistants will receive training to become a new MFL peer mentor. An ‘augmented’ physical activity program has been conceptualised with a clearly defined behaviour change focus and related activities for each week. It can be adapted for 8, 10 or 12 weeks depending on the duration of the particular MFL programme strand. It will not be possible to blind the professional instructors as they will have to learn the techniques developed for the MFL intervention. Final details of the intervention are currently being completed by a multidisciplinary team.

## Outcomes

The primary outcome of the study is to investigate the feasibility of measuring MVPA. The acceptability and safety of the intervention and measurement methods will be investigated. The data will provide reliable estimates for sample size calculation for a future definitive trial. Secondary outcomes relate to data on recruitment, allocation, retention, attrition and attendance. Data will be collected on safety and adverse events will be recorded by the LSP tutor. Participant recruitment outcomes include demographic profile and the success of each of the recruitment strategies. Participant retention outcomes include the number, profile and reasons of participants that drop out. Data will be collected on the numbers who complete each part of the physical activity measures and questionnaires and who wear and return the activPAL devices. Questionnaires will enable the collection of data on healthcare resource use, out-of-pocket expenses and health-related quality of life. For each secondary outcome, the point estimate of effect will be reported, and precision will be presented with 95% confidence intervals. SPSS version 25 will be used for the statistical analyses. At specific time-points, immediately post intervention and 3 months post intervention, follow-up testing sessions will take place. The authors define ‘minimum thresholds’ in the context of the post intervention and 3-month follow up testing as the minimum proportion of participants that attend the testing sessions and provide reliable data.

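### The promise of reliable estimates for the definitive sample size is too strong for the between-hub variance, which eight hubs in three arms can estimate only very imprecisely

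*Protocol article*

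**What the plan says.** The Outcomes section says: "The data will provide reliable estimates for sample size calculation for a future definitive trial". The Methods paragraph of the Abstract is milder. It ties the primary objective to feasibility and data collection, "thereby providing valuable information to guide sample size calculation for a future, more definitive trial".

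Under Study design: "This study will enrol a total of eight hubs and randomise physical activity groups to each of three arms". The allocation under Randomisation process is "true control (two hubs), usual programme (three hubs) or MFL intervention (three hubs", and the same section fixes the unit: "The hubs will be the unit of randomisation and will be randomised to each arm". Study design also says the framework accords with cited guidance on the "minimum number of clusters required to obtain accurate estimates of rates and proportions in pilot and definitive cluster RCTs, respectively".

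The Sample size justification says no formal calculation was done. The size follows from the numbers needed to run programmes: 12 to 15 per programme, four programmes per hub, 48 to 60 per hub, 480 in total and at most 576 after a dropout allowance. The article gives no ICC value and no precision target. ICC appears only in the list of abbreviations.

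**The concern.** The Background describes the trial to follow as a cluster trial. The inputs to its sample size are the individual-level SD of the outcome, the expected loss of data, and the between-cluster variance. The first two are informed by the number of participants, which is large here. The third is informed mainly by the number of hubs, which is eight, and more participants per hub do little for it.

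The Outcomes sentence calls the estimates reliable without separating these inputs. A reader planning the next trial could take the ICC point estimate from these hubs as fit for use. If it were too low, the definitive trial would be badly underpowered. If it were too high, the trial could look impossible to run.

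**Working it through.** **The plan's own figure.** 8 hubs × 4 programmes × 15 = 480, and 480 × 1.20 = 576. Both reproduce. They are recruitment numbers and carry no statement of precision.

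**Inputs.** From the article: 8 hubs, 3 arms (3, 3 and 2 hubs), 48 to 60 per hub, 95% intervals. The 60% rate used below is the complement of the 40% failure limit in Progression criteria. Assumed, because the article gives none: ICC between 0.01 and 0.10.

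**Interval for the ICC.** For a one-way layout with m per hub and an ICC estimate r:

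- F = 1 + m·r/(1 − r)
- F_L = F / F(0.975; df_b, df_w), and F_U = F × F(0.975; df_w, df_b)
- each ICC limit = (F_x − 1)/(m + F_x − 1)

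Here df_b = 8 − 3 = 5 with arm removed, or 8 − 1 = 7 if arm is ignored. The 7 df also apply to baseline data, because randomisation follows baseline collection. With m = 60, df_w = 8 × 59 = 472.

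Worked case, r = 0.05, m = 60, 5 df:

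- F = 1 + 60 × 0.05/0.95 = 4.158
- F_L = 4.158/2.593 = 1.603, so the lower limit is 0.603/60.603 = 0.010
- F_U = 4.158 × 6.029 = 25.07, so the upper limit is 24.07/84.07 = 0.286

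| ICC estimate (assumed) | 95% CI, 5 df | 95% CI, 7 df |
|---|---|---|
| 0.01 | below 0 to 0.126 | below 0 to 0.086 |
| 0.02 | below 0 to 0.171 | below 0 to 0.121 |
| 0.05 | 0.010 to 0.286 | 0.013 to 0.213 |
| 0.10 | 0.032 to 0.430 | 0.037 to 0.340 |

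With 48 per hub and 5 df, an estimate of 0.05 has limits 0.007 to 0.297.

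**Effect on a definitive sample size.** Design effect = 1 + (m − 1) × ICC. At an estimate of 0.05 and 60 per cluster it is 4.0. The limits are:

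- 5 df: 1 + 59 × 0.010 = 1.6 to 1 + 59 × 0.286 = 17.9, a ratio of about 11
- 7 df: 1.8 to 13.6, a ratio of about 8

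If the definitive trial had 15 per cluster, the 5 df limits would give 1 + 14 × 0.010 = 1.14 to 1 + 14 × 0.286 = 5.0, a ratio of about 4.4.

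**Chance of an estimate at or below zero.** This is the probability that an F variate on (df_b, df_w) falls below 1/[1 + m·ICC/(1 − ICC)]. For a true ICC of 0.02 and m = 60, the bound is 1/2.2245 = 0.450. The probability is 0.19 with 5 df and 0.13 with 7 df.

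**Proportions.** Half-width = quantile × √[p(1 − p)(1 + (m − 1)ICC)/(k·m)], with p = 0.60, m = 60 and ICC 0.01 to 0.05:

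- All 8 hubs pooled (t, 7 df = 2.365): 7 to 11 points.
- Three-hub MFL arm (t, 2 df = 4.303): 20 to 31 points. For example, at ICC 0.05, 4.303 × √(0.24 × 3.95/180) = 0.312. With z = 1.96 the range is 9 to 14 points.

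**The case against.** The strongest defence is that the Outcomes sentence names no parameter. The SD of MVPA, completion and attrition are also sample-size inputs, and this design estimates them acceptably when hubs are pooled. The Analysis plan concentrates on interval estimation and treats modelling as exploratory, and the Abstract promises only useful guidance. A feasibility trial need not be powered.

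Much of this stands and limits the point. Three stronger readings are tempting but not supported:

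- **That the plan calls an ICC estimate reliable, or means to use one alone.** It says neither. That the ICC falls within the claim is an inference from hub randomisation and the planned cluster trial.
- **That the plan promises accurate rates within each arm.** Study design refers to rates and proportions without saying by arm, and only as the subject of cited guidance. Whether eight hubs satisfy that guidance cannot be checked from the article. The two-hub control arm would give a nearly useless interval on 1 df, but no progression criterion depends on that arm alone.
- **That the definitive sample size is uncertain 11-fold.** That figure holds for an assumed estimate of 0.05, 60 per cluster and 5 df. It is about 8-fold with 7 df and smaller with smaller clusters.

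The defence does not remove the unqualified word reliable from Outcomes. Planned confidence intervals would display the imprecision but not reduce it. An analysis plan not shown here could not do so either, because the limit is the number of hubs.

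**Conclusion.** The point holds for the between-hub component. As worded, the Outcomes claim covers an input to the definitive sample size that eight hubs in three arms cannot estimate reliably. The conclusion holds over the whole assumed ICC range of 0.01 to 0.10 and with 5 or 7 df; at 5 df it was also checked with 48 per hub. The particular sizes depend on the assumed ICC and cluster size. The intervals assume equal hubs and normally distributed hub effects. The Discussion allows some hubs to run three programmes, so hubs may be smaller and unequal, which does not help.

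The claim is sound for the individual-level SD and for proportions pooled over hubs. It is weaker for the engagement criterion in Progression criteria, which rests mainly on the three MFL hubs. This is a correction of a stated property, not a fault in the trial's size or conduct.

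**What to change.** Reword the Outcomes sentence along these lines: the trial will estimate the individual-level SD of MVPA, and completion and attrition proportions pooled over hubs, with cluster-adjusted 95% CIs; the ICC will be reported with its CI; its point estimate will not be used alone to size the definitive trial, which will be planned over a range of ICCs including external values. A short table of design effects over that range and over plausible cluster sizes would make this concrete.

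Study design needs only a note that the accuracy referred to applies to proportions pooled over hubs, and that a rate in the MFL arm alone will be much less precise.

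The cost is a less favourable stated property and one added table. No extra hubs or participants are needed.
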